## Abstract

**Objective:**

Pain is common and complex for children with intellectual and developmental disabilities (I/DD). Secondary caregivers such as respite workers are lacking important pain‐related information which can impact care. Here, we outline a randomized controlled trial (RCT) protocol testing the effectiveness of a pain training for respite workers supporting children with I/DD.

**Methods/design:**

Organizations enrolled in the RCT were randomly assigned to receive a 3‐3.5 hours pain or family‐centered care training. Data were collected immediately before, after, and 4‐6 weeks following completion of the training. Outcomes are as follows: pain knowledge (primary), pain assessment and management perceptions (secondary), training evaluations (secondary), and use of pain assessment and management skills (tertiary). Both quantitative and qualitative methodologies are being used including questionnaires, rating scales, a standardized vignette, and focus groups.

**Conclusions:**

Results from this trial will be used to further understand the impact of the pain training and inform next steps related to implementation. TRIAL REGISTRATION: ClinicalTrials.gov identifier: NCT03421795.

## INTRODUCTION

1

Pain is common for children with intellectual and developmental disabilities (I/DD)^1^; limited communication skills and differences in pain expression also make assessment and management challenging.^2^, ^3^ There are short‐ and long‐term consequences of inadequately managed pain in those with I/DD including disrupted sleep and reduced adaptive functioning in communication, daily living skills, socialization, and motor skills.^4^, ^5^ There has been progress in assessing pain of children with I/DD using structured behavioral measures such as the *Non‐Communicating Children's Pain Checklist—Revised*
^6^ and self‐report adaptations [eg, 7]. Some work has also been conducted on pain management for children with I/DD. Existing research has alluded to pharmacological, physical, psychological, and process‐related management strategies as important and helpful in a disability context [eg, forms of distraction in a postoperative context: 7, 8].

To date, most work related to pain in children with I/DD has focused on primary caregivers and healthcare providers [eg, 2, 6, 9]. However, secondary caregivers such as respite workers (RW) also spend considerable time with children with I/DD. Initial research addressing this knowledge gap demonstrated that RW who frequently spend time with these children may hold inaccurate beliefs about pain and do not typically have access to specialized pain education related to children with I/DD.^10^ Recent work in related areas (eg, residential support workers of adults with I/DD, school nurses for children with I/DD) has illuminated similar challenges including: inaccurate beliefs,^11^ lack of knowledge,^11^, ^12^ and role confusion with other support staff.^12^ Access to relevant pain knowledge is critical so caregivers of children with I/DD can provide appropriate care.

Recognizing the knowledge gap in the children's respite community, [name], and colleagues^13^ conducted a two‐phase study which first gathered information about RW’s pain‐related experiences and perceived training needs and preferences. This information was used in tandem with extant literature to develop a relevant, empirically informed pain assessment and management training, called *Let's Talk About Pain*, for RW who support children with I/DD. Pilot study results demonstrated (a) increased pain‐related knowledge, (b) increased self‐reported perceptions of the feasibility of and participants’ perceived confidence and skill in pain assessment and management (herein “pain assessment and management perceptions”), and (c) favorable endorsement of the training by RW.^13^ Identified next steps were to systematically evaluate the training's impact on both knowledge and skill use with a larger, more diverse sample and have a longer‐term follow‐up.

This paper presents the complete randomized controlled trial (RCT) protocol used to test the effectiveness and impact of *Let's Talk About Pain* on RW’s pain‐related knowledge, beliefs, and assessment and management approaches when caring for children with I/DD. This paper has been published in advance of the RCT study results to ensure that enough detail regarding the RCT and its development can be available to researchers and clinicians, both of whom could benefit from the information. For example, this information could be important for future RCT implementation, study replication, and application in clinical settings. The *Standard Protocol Items: Recommendations for Interventional Trials (SPIRIT) 2013*
^14^ guideline for the minimum content which should be reported for trial protocols was used to guide protocol content within this manuscript. Additional information not included in the current manuscript is available upon request (eg, copies of consent forms).

## TRIAL STATUS

2

This trial is registered with clinicaltrials.gov (identifier: NCT03421795). Data collection was completed in August 2018; analyses are ongoing. Researchers have no conflicts of interest.

## OUTCOME MEASURES AND HYPOTHESES

3

Participant outcome measures were as follows: (a) pain‐related knowledge [primary], (b) pain assessment and management perceptions [secondary], (c) participants’ training endorsements [secondary], and (d) use of evidence‐based pain assessment and management strategies [tertiary]. Between‐group hypotheses predicted that immediately post and at 4‐ to 6‐week follow‐up, participants receiving the pain training would demonstrate significantly higher pain knowledge and pain assessment and management perceptions compared with the control group. It was also predicted that at follow‐up participants receiving the pain training would have significantly higher levels of evidence‐based pain assessment and management strategy use compared with the control group. Within‐group hypotheses for those receiving the pain training predicted significant increases on pain knowledge and pain assessment and management perceptions from pre to post, with maintenance of these gains from post to follow‐up. It was also hypothesized that participants would provide favorable endorsements of the training program. Finally, significant increases from pre to follow‐up for evidence‐based pain assessment and management strategy use were hypothesized. Results from the RCT are to be published in two separate manuscripts: one reviewing the impact of the training on participant knowledge and perceptions, and the other reviewing participants’ training endorsements and its impact on their strategy use in the workplace.

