### Sample size

4.5

G*Power 3^15^ was used to conduct a power analysis based on our previous *Let's Talk About Pain* training pilot study.^13^ Based on the smallest effect size (*d* = 0.90 [effect size *f* = 0.45]; original range of effect sizes *d* = 0.90‐1.71), a very small sample size (16) was required at power of 0.95 and alpha of 0.05 to detect an overall interaction effect of group by time. A much more conservative effect size (*d* = 0.25 [effect size *f* = 0.1250]) was also used to calculate the most stringent estimate at power of 0.95 and alpha of 0.05, resulting in a total target sample size of approximately 84 participants per group (168 participants total; [15). We aimed for our study sample size to fall in the higher end of this range.

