## ANALYSES

8

Research assistants double enter the data into an SPSS statistical analysis program which is stored on an encrypted, password protected e‐drive. Hard copy data will be stored for seven years after publication of results.

Both intention‐to‐treat (ITT) and per protocol (PP) analysis approaches will be used to analyze the data related to the study's primary and secondary outcomes regarding participants’ pain knowledge and pain assessment and management perceptions; ITT will be primary, and PP will be complementary.^22^, ^23^ After confirming there are no baseline differences between groups, seven 2 × 3 mixed analysis of variances (ANOVA) will be conducted. If statistical assumptions for these analyses are not met, a more conservative approach using bootstrapping will be considered and conducted if the program allows; SPPS has some limitations in this regard.^24^ The dependent variables for the different mixed ANOVAs will be the mean of participants’ pain‐related knowledge (primary outcome measure) and pain assessment and management perception rating scores (secondary outcome measures). In all seven analyses, the within‐subjects factor will be represented by participants’ scores on the related measure across pre, post, and follow‐up time periods, and the between‐subjects factor will be the condition (pain training or control training). In keeping with the study's specific hypotheses, follow‐up analyses using one‐way ANOVAs and paired samples *t* tests will be used as needed to further investigate differences in the dependent variables over time within the pain training group if significant group differences are found.

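### The maintenance-of-gains hypothesis is matched only to tests of difference, and a non-significant difference cannot establish maintenance

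*Protocol article*

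**What the plan says.** Section 3 (Outcome measures and hypotheses) of the protocol article states within-group hypotheses for the pain-training arm. Pain knowledge and the perception ratings are expected to rise from pre to post, "with maintenance of these gains from post to" follow-up. The same section separately predicts that the pain arm will score higher than control both immediately after training and at follow-up.

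Section 8 (Analyses) plans seven 2 × 3 mixed ANOVAs, one for knowledge and six for the perception ratings. For change within the pain arm it names two tools. One is the one-way ANOVA. The other is described as follows: "paired samples *t* tests will be used as needed to further investigate differences in the dependent variables over time within the pain training group". Both are presented as being "In keeping with the study's specific hypotheses" and both carry the same condition, that they are run only "if significant group differences are found". No pair of time points is named. The article states no margin, equivalence or non-inferiority test, or confidence-interval rule for maintenance.

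**The concern.** Maintenance is a claim that nothing material was lost between post and follow-up. A paired t test or one-way ANOVA takes no change as its null hypothesis. It suits the predicted rise from pre to post, where rejecting the null supports the hypothesis. For maintenance the logic is reversed: rejection in the direction of loss counts against it, and failure to reject leaves the question open. Because section 8 presents these tests as serving the stated hypotheses, this is a poor match between hypothesis and method, not merely detail left out of an article.

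The incentive also runs the wrong way. Fewer people at follow-up means lower power, so a non-significant and apparently maintained result becomes more likely. Section 7 (Participant compliance and loss to follow-up) treats retention at that visit as uncertain. At stake is the within-arm statement about durability, for the primary outcome and six secondary ratings. A longer follow-up was one of the next steps that the Introduction draws from the pilot.

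**Working it through.** **The plan's own sample size.** Section 4.5 (Sample size) uses power 0.95 and alpha 0.05 for the group-by-time interaction, with f = 0.45 (d = 0.90) and f = 0.125 (d = 0.25). For a repeated-measures within-between interaction:

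λ = f² × N × m / (1 − ρ), df1 = (k − 1)(m − 1), df2 = (N − k)(m − 1)

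with k = 2 groups and m = 3 times. The article does not give ρ or the sphericity correction; 0.5 and 1 are assumed.

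- f = 0.45, N = 16: λ = 0.2025 × 16 × 3 / 0.5 = 19.44, df 2 and 28. The smallest even N with power of at least 0.95 is 16, as stated.
- f = 0.125, N = 168: λ = 0.015625 × 168 × 3 / 0.5 = 15.75, df 2 and 332. Power is 0.952, as stated (84 per group).

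Both figures reproduce, but they concern the interaction. They do not show what a within-arm comparison of post with follow-up can establish.

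**Power to see a loss from post to follow-up.** Inputs:

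- n = 84, the planned pain arm with everyone retained (section 4.5).
- n = 60, an assumption, because no dropout rate is given.
- Post/follow-up correlation ρ = 0.5 or 0.7, both assumed.
- Two-sided alpha 0.05, no clustering, equal SDs at the two times.

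A loss of d score SDs gives d_z = d / √(2(1 − ρ)) and noncentrality d_z × √n, with n − 1 degrees of freedom. For d = 0.20:

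| n | ρ | d_z | Noncentrality | Power | Non-significant |
|---|---|---|---|---|---|
| 84 | 0.5 | 0.200 | 1.83 | 0.441 | 56% |
| 84 | 0.7 | 0.258 | 2.37 | 0.648 | 35% |
| 60 | 0.5 | 0.200 | 1.55 | 0.332 | 67% |
| 60 | 0.7 | 0.258 | 2.00 | 0.503 | 50% |

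For d = 0.25, power in the same order is 0.620, 0.832, 0.478 and 0.691, so the result is non-significant in 38%, 17%, 52% and 31% of trials.

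**Precision of the change.** The 95% half-width in score SDs is t(0.975, n − 1) × √(2(1 − ρ)/n). In the same order it is 0.217, 0.168, 0.258 and 0.200, a range of about 0.17 to 0.26.

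**Numbers needed to show maintenance against a margin.** The article gives no margin, so these are illustrations. With a true loss of zero, one-sided 0.025 and 80% power, n = 2(1 − ρ) × ((1.960 + 0.842)/margin)²:

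| Margin (SD) | n at ρ = 0.5 | n at ρ = 0.7 |
|---|---|---|
| 0.20 | 197 | 118 |
| 0.25 | 126 | 76 |
| 0.30 | 88 | 53 |

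Whether 84 is enough therefore depends on the margin and the correlation.

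**The case against.** The strongest reply is that the article does not commit the error. A reader might infer that it plans a paired t test of post against follow-up and will take a null result as proof of maintenance. The text supports neither: the tests are to be used as needed, no time points are named, and no rule for reading non-significance is given. That stands, and the point is limited to the mismatch between hypothesis and method. It is also fair that an unseen analysis plan might hold a margin. But the article does name the methods meant to serve its hypotheses, and they are of the wrong kind for this one.

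A reader might also infer that the trial's whole longer-term conclusion rests on absence of evidence. It does not. Section 3 has a between-group hypothesis at follow-up, which a test of difference can properly address. That comparison does not settle maintenance, however, because the pain arm could stay above control after losing much of its gain.

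Two further arguments should not be added. Section 8 makes intention-to-treat primary and does not say that only completers will be analysed. Nor does randomization by organization clearly help the case: if change scores cluster positively and the test ignores it, the standard error is usually too small. With no true change, that gives more rejections and makes maintenance harder to claim.

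Finally, 0.20 SD is about 22% of the smallest pilot effect (0.20/0.90), if both are on the same SD scale. Some would call a gain maintained when 78% of it is kept. That is reasonable, and it is the argument for stating a margin.

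**Conclusion.** The point holds in this limited form: the only methods the article ties to the maintenance hypothesis can count against it but cannot establish it. With 84 pain-arm completers, a true loss of 0.20 SD would go undetected in about 35% to 56% of trials as the correlation moves from 0.7 to 0.5. With 60 completers the range is 50% to 67%. These figures rest on assumed correlations, an assumed completer count and no clustering. They are rates of non-significance; they become rates of wrong conclusions only if 0.20 SD counts as a material loss and non-significance is read as maintenance.

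The mixed ANOVAs and the comparison with control at follow-up are untouched. This is a within-arm matter, worth correcting because the correction needs no new data.

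**What to change.** For the maintenance hypothesis, replace reliance on the difference tests with an estimate: report the pain-arm mean of follow-up minus post, with its 95% confidence interval, for knowledge and each of the six ratings. Claim maintenance only if the lower limit lies above a stated margin of acceptable loss, in QUPID-CR or rating points or as a fraction of the gain from pre to post. The team must fix the margin without reference to the follow-up results.

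Section 2 (Trial status) puts the end of data collection in August 2018, with analysis still under way, so it may no longer be possible to set a margin in that way. In that case, report the change and its interval and make no maintenance claim from a non-significant test.

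The cost is a short change to the analysis text and agreement on a margin. The sample can no longer grow. With half-widths of about 0.17 to 0.26 SD, maintenance will be harder to claim and may stay undecided for some outcomes.

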## DESIGN/METHODS

4

### Study design and procedure

4.1

The RCT represents a multi‐center parallel two group (pain training, control training) design. Data were collected in‐person using hard copy questionnaires immediately before and after an initial training, and again at a 4‐ to 6‐week follow‐up time point using hard copy questionnaires and focus group methodology (See Figure 1 for procedure). Participating organizations were given information about the general purpose of the study as well as the training topic(s), but were not made explicitly aware of whether they were allocated to the control or intervention condition. Participants were told that the purpose of the study was to learn about the impact that training can have on RW knowledge about caring for children with I/DD. No information was provided to participants about study hypotheses.

**FIGURE 1 pne212014-fig-0001:**
[figure not shown]
Outline of study procedures and methodology used for both groups of participants

### Organization recruitment

4.2

Ethical approval was secured from the University research ethics board. Participant recruitment occurred in collaboration with children's respite organizations in Ontario. A researcher‐compiled organization database of 95 potentially eligible organizations developed from (a) a list of respite organizations in Ontario from www.respiteservices.com, and (b) online searches for children's respite services in Ontario was used. These organizations were approached by telephone and/or email. Organizations in closest proximity to the researchers’ home city were contacted first with organizations further away contacted as needed to achieve optimal sample size.

### Randomization

4.3

As organizations agreed to host the program(s) for their RW, the entire organization was randomly assigned to either the control or intervention group. This means that all participating staff from a given organization participated in the same condition. Sequentially numbered, sealed, opaque envelopes (SNOSE) with a 1:1 allocation ratio were created by a research assistant not involved in study recruitment, group allocations, training, or data collection processes. Once assigned, primary investigators were no longer blind to the group allocation.

### Participant recruitment

4.4

Researchers recruited and sought written informed consent from participants at each initial training hosted by participating organizations. Participants had to be proficient in the English language and at least 18 years of age and employed through participating organizations as RW supporting children with I/DD in any setting (eg, family home, community, group homes) in order to participate. Ineligible staff or those who choose not to participate in the study component could still attend the training(s).

### Sample size

4.5

G*Power 3^15^ was used to conduct a power analysis based on our previous *Let's Talk About Pain* training pilot study.^13^ Based on the smallest effect size (*d* = 0.90 [effect size *f* = 0.45]; original range of effect sizes *d* = 0.90‐1.71), a very small sample size (16) was required at power of 0.95 and alpha of 0.05 to detect an overall interaction effect of group by time. A much more conservative effect size (*d* = 0.25 [effect size *f* = 0.1250]) was also used to calculate the most stringent estimate at power of 0.95 and alpha of 0.05, resulting in a total target sample size of approximately 84 participants per group (168 participants total; [15). We aimed for our study sample size to fall in the higher end of this range.

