## PARTICIPANT COMPLIANCE AND LOSS TO FOLLOW‐UP

7

Given the single time point nature of the intervention and previous data from the *Let's Talk About Pain* pilot study,^13^ participant compliance was not of great concern. In contrast, the potential to lose participants at the follow‐up time point was more unknown. Incentives were used during the initial data collection (pre, post) and follow‐up to try to maximize participant retention. Specifically, participants received an entry into a $20 gift card draw (odds of winning: 1 in 25) and refreshments at each visit (ie, at the pre/post data collection date, and at follow‐up), a notebook and pen set at the initial time point, and a certificate along with a $20 honorarium at follow‐up.

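### The stated power of 0.95 at 168 participants assumes independent workers and complete follow-up, although organizations are randomized and follow-up loss was uncertain

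*Protocol article*

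**What the plan says.** The Sample size section of the protocol article describes a G*Power calculation "to detect an overall interaction effect of group by time". It gives two scenarios. With the smallest pilot effect (d = 0.90, f = 0.45), "a very small sample size (16) was required at power of 0.95 and alpha of 0.05". The other scenario is introduced as "A much more conservative effect size", with d = 0.25 and f = 0.125. The section says that this value "was also used to calculate the most stringent estimate at power of 0.95 and alpha of 0.05". The outcome is worded as follows: "resulting in a total target sample size of approximately 84 participants per group", that is 168 in total. The section ends: "We aimed for our study sample size to fall in the higher end of this range".

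The Randomization section says that organizations are the randomized unit, so that "all participating staff from a given organization participated in the same condition". The section on compliance and loss to follow-up contrasts compliance, which caused little worry, with retention: "In contrast, the potential to lose participants" at the follow-up visit was less certain. Its only response is a set of incentives. The Analyses section plans seven 2 × 3 mixed ANOVAs with condition as the between-subjects factor, and makes intention-to-treat primary and per-protocol complementary.

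**The concern.** In a trial that randomizes organizations, workers from one organization share an employer and usually a training session, so their changes over time may be correlated. Such correlation reduces the information in 168 workers. It also ties the error degrees of freedom to the number of organizations and not the number of workers. Loss between the training and the visit 4 to 6 weeks later reduces the information further. If neither enters the calculation, 0.95 describes a different design from the one that was run.

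What is at stake is interpretation. If one of the six secondary ratings shows no difference, a reader may take the stated power as strong evidence against an effect as small as d = 0.25, and the design may not support that.

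**Working it through.** **Inputs from the article.** Two groups (k = 2); three measurements (m = 3); f = 0.125 or 0.45; alpha 0.05; power 0.95; N = 168 or 16. Randomization is by organization.

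**Inputs the article does not give, assumed here.** Correlation between repeated measures rho = 0.5; sphericity (epsilon = 1); ICC 0.01 to 0.10; 10 to 21 workers per organization (the article gives only a cap of 30 per training session); follow-up loss of 20% or 30%. The relevant ICC is that of the change contrasts, because stable differences in level between organizations cancel from a group-by-time interaction.

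**Step 1: reproduce the plan's figures.** For the interaction, λ = f² × N × m / (1 − rho), df1 = (k − 1)(m − 1) = 2 and df2 = (N − k)(m − 1).

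- f = 0.125, N = 168: λ = 0.015625 × 168 × 3 / 0.5 = 15.75, df2 = 332, power 0.952. N = 166 gives 0.9497, so 168 is the smallest balanced total that reaches 0.95.
- f = 0.45, N = 16: λ = 0.2025 × 16 × 3 / 0.5 = 19.44, df2 = 28, power 0.970. N = 14 gives 0.943.

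Both stated figures come out exactly, with nothing added for clustering or loss. Of the correlations tried (0.3 to 0.7 in steps of 0.1, with two or three times), only 0.5 with three times gives both 16 and 168.

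**Step 2: add clustering.** With design effect DE = 1 + (n − 1) × ICC, where n is workers per organization, λ becomes 15.75 / DE. Power falls below 0.95 once DE passes about 1.011. The first block of the table uses df2 = 2 × (168/DE − 2). The second uses organization-level degrees of freedom, df2 = 2 × (J − 2), where J is the number of organizations.

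| Assumption | DE | λ | Power at f = 0.125 |
|---|---|---|---|
| 10 per organization, ICC 0.01 | 1.09 | 14.45 | 0.93 |
| 14 per organization, ICC 0.02 | 1.26 | 12.50 | 0.89 |
| 14 per organization, ICC 0.05 | 1.65 | 9.55 | 0.79 |
| 21 per organization, ICC 0.05 | 2.0 | 7.88 | 0.70 |
| 21 per organization, ICC 0.10 | 3.0 | 5.25 | 0.51 |
| 17 organizations of 10, ICC 0.05, df2 = 30 | 1.45 | 10.86 | 0.81 |
| 12 organizations of 14, ICC 0.05, df2 = 20 | 1.65 | 9.55 | 0.73 |
| 8 organizations of 21, ICC 0.05, df2 = 12 | 2.0 | 7.88 | 0.59 |

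**Step 3: follow-up loss alone, if the ANOVA is run on complete cases.** A 20% loss leaves 134 workers (λ = 12.56) and power of about 0.89. A 30% loss leaves about 118 (λ = 11.06) and power of about 0.85.

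**Step 4: sensitivity to the correlation.** With no clustering, rho = 0.3 gives 0.86 at 168 and rho = 0.7 gives above 0.99. At DE 1.65, rho = 0.7 gives 0.95; at DE 2.0 it gives about 0.91.

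**Step 5: the pilot effect.** At f = 0.45 and DE 3.0, λ = 0.2025 × 168 × 3 / 0.5 / 3 = 68.04, and power is above 0.99. It stays above 0.99 with a further 30% loss and degrees of freedom for only eight organizations.

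**The case against.** Four points can fairly be made for the plan.

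- **The size of the shortfall is not known.** The article gives no correlation, ICC, number of organizations or organization size. In a mild case the loss is under two percentage points, and a correlation of 0.7 would offset a design effect of 1.65. This stands. A reader might infer that the design cannot reach 0.95 at all, or that power is certainly down at 0.5 to 0.8. The article supports neither; the direction is secure, the size is not.
- **The trial may have ample power.** The calculation starts from pilot effects of d = 0.90 to 1.71, and 168 was chosen with a much smaller effect in mind. At f = 0.45 none of the penalties considered here matters. This also stands: it would be wrong to conclude that the trial is underpowered for the effect seen in the pilot.
- **The ANOVA may not be restricted to completers.** A mixed ANOVA is often run that way, but the Analyses section does not say so and makes intention-to-treat primary; handling of missing scores may be set out elsewhere. The figures for loss are therefore conditional on complete-case analysis.
- **An article condenses.** A design effect might have been left to a fuller document. This does not stand: 16 and 168 reproduce exactly without one, so under these settings an unstated allowance would have produced a larger total.

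Nor is the arithmetic itself faulty. It is right for individually randomized, fully observed participants; what is wrong is applying it to this design without qualification.

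**Conclusion.** The point holds as a limited one. The pairing of 168 participants with power 0.95 at d = 0.25 is a result for independent, fully observed workers. At the correlation of 0.5 that reproduces the plan's figures, it carries over to this organization-randomized trial only if the ICC of the change contrasts is close to zero and almost nobody is lost. Under the assumed ranges, power with 168 lies between about 0.93 and 0.51 before organization-level degrees of freedom are applied. With them, at ICC 0.05, it is about 0.81 (17 organizations of 10) to 0.59 (8 of 21). Loss of 20% or 30% alone gives about 0.89 or 0.85 on complete cases. The description of 168 as the most demanding estimate is not justified, since it rests on the two most favourable assumptions available. The consequence is confined to effects near d = 0.25, chiefly the reading of a null result on a secondary rating.

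**What to change.** Do not enrol more participants; the Trial status section says that data collection is complete and analyses are ongoing. Replace the 0.95 statement with a short table of power at f = 0.125, conditional on a stated correlation between repeated measures, ICC of the change contrasts (for example 0.01, 0.05 and 0.10) and follow-up loss (0%, 20% and 30%). Use the actual number and size of organizations, with organization-level degrees of freedom. State whether the figures for loss assume complete-case analysis. Stop describing 168 at 0.95 as the most stringent estimate, and add that power at the smallest pilot effect remains above 0.99.

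The cost is a brief recalculation, a few lines of text and a less favourable stated power.
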